## Abstract

Spatial navigation (SN) has been reported to be one of the first cognitive domains to be affected in Alzheimer’s disease (AD), which occurs as a result of progressive neuropathology involving specific brain areas. Moreover, the epsilon 4 isoform of apolipoprotein-E (APOE-ε4) has been associated with both sporadic and familial late-onset AD, and patients with mild cognitive impairment (MCI) due to AD are more likely to progressively deteriorate. Spatial navigation performance will be examined on a sample of 76 community-dwelling senior citizens (25 healthy controls; 25 individuals with subjective cognitive decline (SCD); and 26 patients with MCI due to AD) via a virtual computer-based task (i.e., the AppleGame) and a naturalistic task (i.e., the Detour Navigation Test—modified version) for which a wearable device with sensors will be used for recording gait data and revealing physiological parameters that may be associated with spatial disorientation. We expect that patients with MCI due to AD and APOE-ε4 carriers will show altered SN performances compared to individuals with SCD and healthy controls in the experimental tasks, and that VR testing may predict ecological performance. Impaired SN performances in people at increased risk of developing AD may inform future cognitive rehabilitation protocols for counteracting spatial disorientation that may occur during elders’ traveling to unfamiliar locations. The research protocol has been approved by the Ethics Committee of the Istituto Auxologico Italiano. Findings will be published in peer-reviewed medical journals and discussed in national and international congresses.

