### 1.3. Spatial Navigation in Alzheimer’s Disease

AD is a multifactorial neurodegenerative disease, resulting from complex interactions between genetic and environmental factors, that remains the leading cause of dementia to date. The proportion of people aged 65 years and over is growing rapidly worldwide, and it is estimated that by 2060, this age group will account nearly for 24% to 29% of the population in Western Europe and the United States [27], representing a health emergency due to social and sanitary costs. AD is characterized by progressive deterioration of cognitive functions, with episodic memory loss and spatial disorientation as the main hallmarks. No causal therapies for AD are currently available, although drug treatment efforts are progressing [28]. Thus, advances in biomarkers and behavioral tests for identifying individuals at increased risk of developing AD represent a crucial target of current research and therapeutics. Spatial navigation, or the ability to determine and maintain a trajectory from one place to another, gradually declines in the course of physiological aging [29,30,31], and spatial disorientation (SD) represents a core feature of pathological aging, especially AD [32]. Although cognitive decline precedes overt AD, pathological changes may even begin years before there are any overt behavioral impairments, and new treatments are being sought to modify this process [33]. Indeed, it has been proposed that subjective cognitive decline (SCD) (i.e., a self-experienced decline without objective cognitive impairment) might appear at the end of the preclinical phase of AD [34]. SN complaints are frequent symptoms not only in AD but also in SCD and MCI, and can be detected by specifically designed questionnaires [35] or by virtual and real-world navigation tasks [36]. SCD is gaining increased prominence in neurodegenerative research as a potential marker for future mild cognitive impairment (MCI) due to AD [37], a condition that represents the prodromal state of dementia associated to the disease. Approximately 90% of MCI patients with pathologic cerebrospinal fluid biomarker levels at baseline develop AD within 9 to 10 years [38]. Deficits in spatial orientation appear early in the course of the AD continuum [16]. AD is mainly characterized by the presence of beta-amyloid protein plaques and neurofibrillary tangles of hyperphosphorylated tau protein. According to Laczó et al. [7], amyloid-β accumulation first emerges in the neocortical regions and, early on, affects the retrosplenial cortex, while tau pathology first emerges in the transentorhinal cortex (Braak stage I) and spreads to the posteromedial entorhinal cortex and the hippocampus (Braak stage II and III) and finally to the posterior cortical regions (Braak stage IV). Neurodegeneration and brain atrophy parallel the pattern of tau pathology spreading [39]. Degeneration of the entorhinal cortex as a critical brain district supporting SN represents an initial stage of typical AD [40], and a profound loss of its neurons occurs in very mild AD [41]. Neurofibrillary AD pathology in the entorhinal cortex and hippocampus also represent the neuropathological substrate of memory decline [42] and defective PPI [43]. Finally, tau abnormalities in the entorhinal cortex can already be observed in adults under the age of thirty [44], especially in those carrying the Apolipoprotein-E(APOE)-ε4 allele [45].

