## 2. Materials and Methods

### 2.1. Design, Study Population, Recruiting Centers and Trial Registration

This is a multi-center prospective observational study. A sample of outpatients with SCD and MCI due to AD will be enrolled from three sites in Lombardy (Italian Region): “San Gerardo” Hospital (Monza), “Luigi Sacco” University Hospital (Milan), and Fondazione IRCSS Ca’ Granda Ospedale Maggiore Policlinico (Milan, Italy).

Individuals with SCD will be detected according to Jessen and colleagues’ criteria [79] while prodromal AD will be defined according to Dubois and colleagues’ criteria [80], respectively. Healthy older adults will be enrolled through advertisements distributed in social centers for senior citizens in Milan (Italy) and through popular science events (conferences, webinars) concerning research in AD prevention. The three sites currently use the neuropsychological batteries reported in the Appendix A. Healthy older adults will be assessed by the experimenters at the Department of Psychology, Catholic University (Milan, Italy), by adopting the same neuropsychological battery as the IRCSS Ca’ Granda Ospedale Maggiore Policlinico (Milan, Italy). Family medical history of AD was collected during clinical interview along with laboratory tests results and neuroimaging findings for outpatients with SCD and MCI due toAD.

For the whole sample, inclusion criteria will involve the following: age from 65 to 85 years; education not less than 5 years; basic ICT skills. All participants will be excluded from the study according to the presence of visual, hearing, or motor impairment significantly interfering with SN tasks; neurological/psychiatric disease or other medical conditions preventing SN; history of alcohol or drugs addiction; intake of psychotropic drugs; and presence of dementia. Recruitment will end on 29 February 2024.

With the aim of obtaining results that can be generalized, sociodemographic and clinical features of the sample to be recruited will be analyzed among the research team members prior to the sample enrollment according to epidemiological studies carried out on the Italian elderly population, specifically including MCI patients [81,82,83] and individuals with SCD [84].

The Uniform Resource Locator for the clinical trial registration is the following one: https://classic.clinicaltrials.gov/ct2/show/NCT05944601 (identifier: NCT05944601) (accessed on 13 July 2023).

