### 2.4. Statistical Analysis

Data distribution will be first checked on collected variables by assessing skewness and kurtosis values, by performing normality and heteroscedasticity tests, and by visually inspecting histogram and Q–Q plots. Based on data meeting or non-linear model assumption, either parametrical or non-parametrical analyses will be performed. By means of the R marco *pwr* [86], the minimal sample size has been set as 76 participant, based on a power analysis for a multiple regression model that took into account the following parameters: α = 0.05; 1-β = 0.9; *f*^2^ = 0.15 (medium effect size, in order to be conservative) [87]; and numbers of predictors: 3 (age, APOE genotypes, and belonging to each group, with the last two predictors as dummy variables).

We will detect the route disorientation scores, i.e., WTs and MsH, as already described in Puthysserypaddy et al. [64]. Accordingly, all the violations in terms of deviations from the pre-established return path (i.e., movement at an intersection onto a different path as compared to the original one, or non-roadable walkways) will be written down by the experimenter as WTs in a pre-set paper grid for *Route A*. The overlaps with the *Route A* return path, and, likewise, non-roadable walkways will be written down by the experimenter as WTs in a pre-set paper grid for Route *B*. Further, we will detect the MsH as the participant either slows down/stops and looks around to aid orientation or verbally admits to the experimenter that he/she is unsure about his/her whereabouts, both for *Route A* and the *Route B* return path.

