## Appendix A

**Table A1 jpm-14-00192-t0A1:** Neuropsychological tests used in the recruiting centers.

	“San Gerardo” Hospital Monza, Italy	“Luigi Sacco” Hospital Milan, Italy	Policlinico Hospital, Milan, Italy
**Global cognition**	Mini Mental State Examination (Magni et al., 1996) [98]	Mini Mental State Examination (Foderaro et al., 2022) [99] or Montreal Cognitive Assessment (Aiello et al., 2022) [100]	Mini Mental State Examination (Magni et al., 1996) [98]
**Memory** ** *Short-term memory auditory–verbal* **	Digit span backward (Monaco et al., 2013) [101] Digit span forward (Monaco et al., 2013) [101]		Digit Span Backward (Monaco et al., 2013) [101] Digit Span Forward (Monaco et al., 2013) [101]
** *Visuospatial* **			Corsi Span Backward (Monaco et al., 2013) [101] Corsi Span Forward (2013) [101]
** *Long-term memory auditory–verbal* **	List of semantically related words (Mauri et al., 1997) [102]	Free and Cued Selective Reminding Test (Girtler et al., 2015) [103]	Pairs Associate Learning (Normative data of the Hospital) Memory of prose (Normative data of the Hospital)
** *Visuospatial* **	Rey–Osterrieth Complex Figure (Caffarra et al., 2002) [104]—recall Corsi learning suvra-span (Spinnler e Tognoni, 1987) [105]	Rey–Osterrieth Complex Figure (Caffarra et al., 2002) [104]—recall Corsi learning suvra-span (Spinnler e Tognoni, 1987) [105]	Corsi learning suvra-span (Spinnler e Tognoni, 1987) [105]
**Language** ** *Comprehension* **	Neuropsychological Examination for Aphasia (ENPA)—words and sentences comprehension test (Capasso and Miceli, 2001) [106]		Token Test (Spinnler e Tognoni, 1987) [105]
** *Naming* **		Naming colored pictures (Catricalà et al., 2013) [107] Naming figures (Catricalà et al., 2017) [108]	Naming colored pictures (Catricalà et al., 2013) [107]
** *Fluency* **	Phonemic Fluency Test and Semantic Fluency Test (Costa et al., 2014) [109]	Phonemic Fluency Test and Semantic Fluency Test (Costa et al., 2014) [109]	Phonemic Fluency Test and Semantic Fluency Test (Costa et al., 2014) [109]
**Visual–constructive skills** **Visual–perceptive functions**	Rey–Osterrieth Complex Figure (Caffarra et al., 2002)—copy [104]	Clock Drawing Test (Caffarra et al., 2011) [110] Rey–Osterrieth Complex Figure (Caffarra et al., 2002)—copy [104]	Clock Drawing Test (Caffarra et al., 2011) [110]
**Visual agnosia**			Street’s Completion Test (Spinnler e Tognoni, 1987) [105]
**Constructive apraxia**			Constructive Apraxia Test (Spinnler e Tognoni, 1987) [105]

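### SCD and MCI are diagnosed at three hospitals through different test batteries, and no analysis the article names includes recruiting centre, so the SCD-MCI contrast can absorb site differences

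*Protocol article*

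**What the plan says.** Section 1.7 makes the comparison of controls, SCD and MCI the first endpoint. The Abstract gives the planned groups as "25 healthy controls; 25 individuals with subjective cognitive decline (SCD); and 26 patients with MCI due to AD".

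Section 2.1 recruits the SCD and MCI outpatients from three hospitals. It names one published criteria set for SCD and one for prodromal AD, and has laboratory and imaging findings collected for these patients. It then states: "The three sites currently use the neuropsychological batteries reported in the Appendix A". Controls are recruited through advertisements and public events, and are tested at the university with the Policlinico battery.

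Section 1.3 describes SCD as "a self-experienced decline without objective cognitive impairment". Appendix A lists these long-term verbal memory tests:

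- San Gerardo: a list of semantically related words.
- Sacco: a free and cued selective reminding test.
- Policlinico: paired associates and prose memory, both on in-house norms (the second entry begins "Memory of prose (Normative data of the Hospital").

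Section 2.4 gives the regression behind the sample size as "numbers of predictors: 3 (age, APOE genotypes, and belonging to each group", the last two coded as dummies. The gait and questionnaire comparison of the three groups is a one-way ANOVA without covariates. The other named analyses are correlations, and regressions of wrong turns and hesitations on drop error. Section 2.4 acknowledges that batteries differ between centres. Its remedy, grouping tests by domain and dichotomising the scores, applies to the correlations with the neuropsychological tests.

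**The concern.** Group is the exposure of the first endpoint. If SCD means complaints without objective impairment, the line between SCD and MCI depends partly on test results, and those tests and norms vary by hospital. Section 1.5 calls episodic memory loss the long-standing gold standard for diagnosing cognitive impairment due to AD, and the verbal long-term measures of it are what no two sites share.

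Two things could follow. Sites might supply SCD and MCI in different proportions, so that differences in catchment or severity between hospitals appear as a group difference. Sites might also set a different effective threshold, so that the labels do not mean the same thing everywhere. The article recognises the battery difference for the exploratory correlations but not for the group variable.

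**Working it through.** **The plan's sample size.** Section 2.4 says "the minimal sample size has been set as 76 participant", from "α = 0.05; 1-β = 0.9" and f² of "0.15 (medium effect size, in order to be conservative". An overall F test of 3 predictors needs N = 99 for power 0.90 and N = 77 for 0.80; power at 76 is 0.796. A 1-df test at power 0.90 needs 71 residual df, so 71 + 4 + 1 = 76 with four coefficients. The article does not say which test is meant. The present point does not depend on it; only the group sizes are used below.

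**Overlap of the batteries (Appendix A).**
- Long-term verbal memory: different at every site.
- Digit span (short-term verbal): San Gerardo and Policlinico only.
- Corsi supra-span (long-term visuospatial): all three sites.
- MMSE, visual search and Colored Progressive Matrices: Sacco cites different normative sources from the other two. (For global cognition Sacco may use the MoCA instead of the MMSE.)
- Frontal Assessment Battery: norms differ between San Gerardo and the Policlinico; it is not listed at Sacco.

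**Assumptions.** The article gives no SCD and MCI counts by site and no site offset. I assume 51 outpatients (25 SCD, 26 MCI), 17 per site, an outcome SD of 1 within group and site, site offsets of +s/2, 0 and −s/2, and no true SCD-MCI difference.

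**Bias.** With MCI shares of 80/50/20%, the nearest counts are MCI 14/9/3 and SCD 3/8/14.
- MCI mean offset: (14 − 3)/26 × s/2 = 0.212s.
- SCD mean offset: (3 − 14)/25 × s/2 = −0.220s.
- Spurious difference: 0.432s, which is 0.22 SD at s = 0.5 and 0.35 SD at s = 0.8.
- Standard error of the unadjusted difference: about √(1/25 + 1/26) = 0.280 SD.

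With 60/50/40% shares (MCI 10/9/7, SCD 7/8/10), the same sum is (3/26 + 3/25) × s/2 = 0.118s, or 0.06 to 0.09 SD.

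**False-positive rate.** Simulated two-sided 5% tests of SCD versus MCI, with the shares taken as each outpatient's probability of being MCI:

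| MCI shares by site | s = 0.5 to 0.8, no centre term | with centre |
|---|---|---|
| equal | about 5% | about 5% |
| 60/50/40% | about 5% to 6% | about 5% |
| 70/50/30% | about 7% to 11% | about 5% |
| 80/50/20% | about 10% to 19% | about 5% |

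Fixing the counts at 14/9/3 moves the top figure to about 21%. With 80/50/20% shares but s = 0.25, the rate is about 6% to 7%.

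**Cost of the centre term at 14/9/3.**
- Group variation in total: 26 × 25/51 = 12.75.
- Group variation within sites: (14×3 + 9×8 + 3×14)/17 = 9.18.
- Variance inflation: 12.75/9.18 = 1.39.
- At an assumed d = 0.8, the noncentrality falls from 0.8/0.280 = 2.86 to 2.86/√1.39 = 2.42, and power from 0.80 to 0.66. With shares as probabilities it falls from about 0.78 to 0.64.

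Under a stronger imbalance (SCD 18/5/2, MCI 2/6/18) it falls from 0.80 to 0.50.

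**What a centre term does not repair.** If a fraction e of each group is mislabelled, the observed effect is d(1 − 2e). At d = 0.8, e = 0.10 gives 0.64 (power 0.61) and e = 0.20 gives 0.48 (power 0.39), against 0.80 with no mislabelling.

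**The case against.** A reader might infer that each hospital decides who is SCD and who is MCI by its own battery alone. Section 2.1 does not say that. It names one criteria set per diagnosis for all sites, and laboratory and imaging findings are collected too. The sentence about the batteries reports current use and is not an allocation rule. The description of SCD as decline without objective impairment comes from the Introduction. What remains is that shared criteria applied through unshared tests and norms leave room for different thresholds, and the article states no common cut-off or central adjudication.

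It would also be too broad to say that no verbal memory test is shared, since two sites list digit span. Nor can a share of discordant diagnoses be computed: that would treat diagnosis as one test with one cut-off, a rule the article never states.

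The strongest objection is that confounding is possible, not shown. No counts by site are given, and balanced or mildly unequal mixes leave the error rate near 5%. Outcomes are obtained under common conditions: the AppleGame under the experimenters' supervision and the detour test in one garden. A site effect could therefore enter only through case mix or labelling. This objection stands and limits the claim to what can happen.

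Finally, the list of age, APOE and group belongs to the power calculation, and a full analysis plan, not shown, might add centre. The article therefore does not exclude centre. But it does name its models, centre is in none of them, and it limits its remedy for the battery difference to the correlations.

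**Conclusion.** The point holds in conditional form. The batteries and some norms differ by hospital, no long-term verbal memory test is common to all three, and no named analysis includes centre. The SCD-MCI contrast can therefore absorb site differences, provided that the SCD:MCI mix or the effective threshold varies by site. The article does not establish that either does.

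The inflation is negligible under balanced or mildly unequal mixes, and material only when a marked imbalance coincides with a site spread of half an SD or more. Those shares and offsets are my assumptions, with no source in the article. This is an inexpensive improvement to the stated analysis and does not show that the planned comparison is invalid.

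**What to change.** Change section 2.4 as follows:

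1. Include recruiting centre (two dummy variables) in the SCD-versus-MCI comparisons, and report each result with and without it.
2. Add a sensitivity analysis limited to the controls and the Policlinico outpatients, who share one battery.
3. State that contrasts with controls cannot be centre-adjusted, because controls come from outside the three hospitals. State also that a centre term removes site offsets but does not correct site-dependent misclassification.

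This needs no new data. The centre term costs 2 degrees of freedom and more power the more unequal the sites are, which is also when the unadjusted result is least trustworthy; hence the request for both. The same-battery subset will be imprecise: with about 17 outpatients split 9 versus 8, power at d = 0.8 is about 0.34, so it can show only whether the estimate points the same way.

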### 2.2. Genetic and Psychological Evaluation

All participants will be genotyped for the APOE polymorphisms by collecting genetic material extracted from buccal brushes using the Gentra Puregene^®^ (40723, Hilden, Germany) specific assay. The collected samples will be analyzed in the Neuropathology and Clinical Neurobiology Laboratory of “San Giuseppe Hospital” in Piancavallo (Verbania, Italy), IRCCS Istituto Auxologico Italiano. All participants will be blinded towards APOE genotype.

Subjective strategies of SN and personal satisfaction for wearable technology will be evaluated via the Subjective Spatial Navigation Complaints (SSNC) questionnaire [35] and the Tele-healthcare Satisfaction Questionnaire (TSQ-WT) [85], respectively, which have previously undergone a back-translation process for Italian culture adaptation.

### 2.3. Experimental Navigation Tasks

#### 2.3.1. Virtual Navigation Test

In a comfortable and silent room under the experimenters’ supervision, all participants of the research will first perform the short version (i.e., 56 trials) of a computer-based SN task, i.e., the AppleGame [43], specifically designed by the researchers for older adults (≥65 years) as a measure of virtual PI. This VR task comprises 8 practice trials followed by 16 trials for each of the three subtasks. They differ with regard to the presence or absence of supportive spatial cues: the PPI subtask without any supportive cue; the boundary PI (BPI) subtask with a circular boundary; and the landmark PI (LPI) subtask with an intra-maze landmark (e.g., a lighthouse) close to the center of the virtual circular arena (please see Figure 1 in [43] for a complete representation of the experimental paradigm). For each trial, the participants have to collect a basket (i.e., start phase) and try to remember its location (i.e., the goal location). After a navigation phase toward a variable number of trees (1 to 5, i.e., “the outgoing phase”) which disappear after having been reached, the participants have to find their way back to the goal location (i.e., “the incoming phase”) after they have collected an apple under the last tree. The “outgoing distance” and the “incoming distance” will be recorded. Path integration performance for each subtask will be assessed as the distance between the correct goal location and the response location, i.e., the drop error, constituting the score of the “AppleGame”.

#### 2.3.2. Naturalistic Navigation Test

All participants will then undergo a modified version of the “Detour Navigation Test” (DNT-mv) [64] in a naturalistic environment, i.e., an urban park. In contrast to the original one, the version we created takes into account the fact that our participants do not present with dementia; they retain some ability to navigate in urban unfamiliar environments in comparison to AD patients, for which the exploration of places outside home is very critical [25]. The DNT-mv will be performed in the outdoor garden of the Pontificio Istituto Missioni Estere—PIME ([name]), a 1000 m^2^ arena (20 × 50 m^2^) (Figure 4), in order to guarantee that MCI patients, SCD individuals, and healthy elderly controls have a safe environment to explore. The experimenter and his staff consisting of clinical psychologists will follow the elderly participants for their safety, providing instructions for the tasks to be performed without giving any feedback on the participants’ correctness.

The participants are asked to complete a path from a start point (Figure 4, green point) to a destination point (Figure 4, blue point) in *Route A* (80.5 m) (Figure 4, dotted red line, on a scale of 1 to 500) in the PIME outdoor garden under the experimenter’s guidance. An interfering cognitive task mimicking distracting urban stimuli (e.g., people chattering, cars horns, background noise, pedestrian crossing, recognizing someone on the street, receiving a phone call, etc.) will be provided by a smartwatch worn by the participants, who are required to touch the screen when it displays a specific colored shape among different shapes presented with an interval of 15 s from each other. During this path, they are also required to remember all the existing landmarks as a cognitive exercise useful for the evaluation of spatial episodic memory. Once at the destination, they are asked to put in order the encountered landmarks (Figure 5), randomly presented as a written naming list on the experimenter’s smartphone App. In case of a sudden technology breakdown, an algebraic calculation (i.e., “*Please, subtract 7 from 100 and keep going until I stop you*”) and a different landmarks reordering (i.e., presentation with flash cards) will be provided by the experimenters as replacements. The landmarks will be mixed up with distractors in order to detect hits and false alarms. Then, they are required to navigate back to the original start point using the same route. This first task requires participants to predominantly utilize an egocentric strategy based on a navigator-centered representation of the environment.

Later, the participants will be required to reach the destination point of the encoded *Route A* again. However, at the first intersection of the way back (Figure 4, purple asterisk), unknown to them, they will be asked to find an alternative route to come back (*Route B^1^*, 94 m; *Route B^2^*, 78.5 m; *Route B^3^*, 74 m) that does not overlap with *Route A* at all (Figure 4, dotted black lines). This second task requires participants to predominantly utilize an allocentric strategy based on a formed cognitive map of the garden.

Before the navigation of the urban garden, all participants will equip the Howdy Senior^©^ (Comftech S.r.l., Monza, Italy) device (Figure 6), a wearable monitoring system. All participants will be recorded according to cardiac and respiratory parameters *at rest* for five minutes and during the naturalistic experiment (Table 1). These data will be available thanks to the instant reports produced by the connected “Howdy Senior App” set up on the experimenter’s smartphone.

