## 3. Discussion

In relation to the first endpoint, we expect that patients with MCI due to AD will show significantly more SN deficits than healthy controls and individuals with SCD, both in the AppleGame and in the DNT-mv, in terms of higher drop errors on BPI, LPI, and PPI and higher amounts of WTs and MsH, respectively. Virtual and ecological deficits may reflect a cognitive inefficiency of the entorhinal cortex, where AD neuropathology manifests early [25]. It has also been demonstrated that virtual and ecological SN tasks can detect the SN alteration of amyloid-positive MCI patients [89,90]. According to Colmant et al. [91], we also presume that APOE-ε4 carriers will report a PPI deficit in the VR task differently from non-carriers, regardless of subgroup.

Furthermore, we also anticipate that significant physiological parameters modifications (particularly, respiratory function) may be particularly associated with MsH, given that anxiety rather than depression significantly influences SN abilities in non-demented elders [92]. Starting from difficulties in spatial orientation evaluated in naturalistic experiments able to modify gait [93], we finally assume that patients with MCI due to AD will perform worse than SCD and healthy controls in terms of “Time” and “Speed”, and report significant differences in “Direction”, all variables collected by the Howdy Aptive app in the open-space naturalistic task.

In relation to the second endpoint of the research, we assume that the drop errors obtained in the VR task may predict the route disorientation scores of the naturalistic task. In particular, we expect a causal relationship between the BPI drop error of the AppleGame and the *Route A* return path of the DNT-mv, as well as between the LPI drop error of the AppleGame and the *Route B* return path of the DNT-mv, because they mainly rely on egocentric and on allocentric navigation, respectively. A recent systematic review and meta-analysis [44,94] has outlined that the association of navigational tasks performed in virtual and real environments needs to be deeply clarified. In light of this, we believe that the AppleGame could represent a validated technique with which to detect, in laboratory, early SN deficits in populations at risk of dementia conversion to provide high-quality, time-limited diagnosis. It is a cost-effective tool able to predict real-life SN impairment that should be routinely used in clinical practice.

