However, our research protocol presents some limitations. Urban park conditions (e.g., presence of potential distractors) might influence the performance of the study participants in the naturalistic task, and the technology used may breaks down in relation to the GPS signal power. Moreover, the frequency of APOE-ε4 carriers, especially in patients with MCI due to AD, may be unsatisfactory due to specific demographical variables of our European country [95]. Although the APOE-ε4 represents the strongest genetic risk factors for AD [54], as genetic research has proceeded, studies have found suggestive links between late-onset AD and a number of other genes, such as ABCA7, CLU, CR1, PICALM, PDL3, TREMZ, and SORL1 [96,97], which might be relevant in influencing SN performances, too.

Nevertheless, we first estimate the impact of the present research project in terms of an innovative technological SN assessment in senior citizens at high risk of developing AD dementia, with relevant implications for maintaining independent spatial orientation in daily life activities. In fact, this kind of smart technological apparatus (i.e., a body T-shirt with sensorial devices and a smartphone with digital health Apps) is able to alert caregivers when their loved ones with cognitive decline are required to navigate unfamiliar locations alone, and it constitutes a potential means of remotely monitoring them.

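### The breakdown fallback on Route A swaps in a heavier distractor and a different landmark test, so affected participants may not be comparable; likely a small effect, cheaply avoided

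*Protocol article*

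**What the plan says.** Section 2.3.2 describes the guided outward walk on Route A, 80.5 m long. A smartwatch supplies an interfering task meant to imitate urban distraction: participants must "touch the screen when it displays a specific colored shape among different shapes presented with an interval of 15 s from each other". The same walk is the learning phase: "During this path, they are also required to remember all the existing landmarks as a cognitive exercise useful for the evaluation of spatial episodic memory". At the destination they order the landmarks, which are "randomly presented as a written naming list on the experimenter’s smartphone App", mixed with distractors so that hits and false alarms can be counted. They then walk back by the same route. Later they go to the destination again and are asked for a detour on the way back (Route B).

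For a sudden technology breakdown the section names two substitutes. The distractor becomes an instruction from the experimenter: "Please, subtract 7 from 100 and keep going until I stop you". The written list is also exchanged: "a different landmarks reordering (i.e., presentation with flash cards) will be provided by the experimenters as replacements".

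Section 2.4 scores wrong turns (WTs) and moments of hesitation (MsH) on the Route A and Route B return paths. Cardiac and respiratory data are recorded at rest and during the naturalistic experiment (section 2.3.2), and nothing in that description excludes the outward leg.

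**The concern.** A backup procedure should yield the same measurement by other means. Here it changes the task. The planned distractor asks for occasional detection of a target. The substitute asks for unbroken mental arithmetic while the participant is learning the route and landmarks. Section 1.2 itself says that attention, working memory and executive function may be critical to navigation, so by the plan's own reasoning the difference in load matters. The substitute landmark test is called different by the article itself.

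The risk is that some participants' scores reflect the mode of testing as well as navigation ability. If the heavier task costs more in patients with MCI, this would add to the group difference that the Discussion expects.

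**Working it through.** The plan gives no breakdown rate and no equivalence figure, so there is nothing of its own to reproduce. The check has three steps.

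**Inputs.** From section 2.3.2: Route A length 80.5 m, shape interval 15 s, subtraction of 7 starting at 100. From the Abstract: groups of 25, 25 and 26. Assumed, because the article does not give them: walking speed *v*, the share *q* of a group on the fallback, and the fallback's effect *d* in SD units.

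**Step 1: load of the two distractors.** Walk time *t* = 80.5 / *v*; shapes shown = *t* / 15.

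| Assumed speed (m/s) | Time (s) | Shapes shown |
|---|---|---|
| 0.6 | 134.2 | 8.9 |
| 0.8 | 100.6 | 6.7 |
| 1.0 | 80.5 | 5.4 |
| 1.2 | 67.1 | 4.5 |

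At 0.8 to 1.2 m/s that is about 4 to 7 shapes, with a response only to targets. Serial sevens runs continuously and allows 14 subtractions before it is exhausted (100 − 14 × 7 = 2). Someone averaging a subtraction every 4.8 s (67.1 / 14) at the faster pace, or every 7.2 s (100.6 / 14) at the slower one, finishes just as the walk ends. Anyone quicker runs out early. The load is therefore heavier than planned and also varies between people.

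**Step 2: which measures it can reach.**
- *Landmark order, hits, false alarms:* directly, through load while learning and possibly through format at test.
- *Gait and cardiorespiratory data on the outward leg:* directly. The gait ANOVA and the step-variability correlations in section 2.4 are not stated to exclude that leg. If answers are given aloud, which the wording suggests but does not state, breathing would plausibly change.
- *WTs and MsH:* only indirectly. They are scored on return paths, after the distractor walk. For Route B the link is weaker still, because the participant has by then walked back along Route A and gone out again.

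**Step 3: possible bias between two groups.** Bias = *q*₁*d*₁ − *q*₂*d*₂.
- Equal use, equal effect: 0.
- Unequal use, equal effect: 0.3 × (0.20 − 0.10) = 0.03 SD, up to 0.8 × (0.30 − 0.10) = 0.16 SD.
- Equal use, unequal effect: 0.10 × 0.3 = 0.03 SD if the effects differ by 0.3 SD; 0.20 × (0.8 − 0.3) = 0.10 SD if they are 0.8 and 0.3 SD.

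Even without bias, mixing the modes adds noise. Variance within an affected group is multiplied by 1 + *d*²*q*(1 − *q*), which runs from 1 + 0.09 × 0.09 = 1.008 to 1 + 0.64 × 0.21 = 1.134. In a group of 25, each affected participant is 4% of the group.

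**The case against.** The best defence is that this is a contingency of unknown frequency that may touch hardly anyone. That stands, and it limits the severity.

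Several stronger readings are tempting, and the documents do not support them:
- *That breakdown of these tasks is expected to be common.* The Discussion does warn that "the technology used may breaks down in relation to the GPS signal power", but GPS serves the Aptive tracking data. Nothing links GPS loss to the watch display or the landmark list.
- *That breathing during hesitation is directly distorted.* The Discussion expects that "significant physiological parameters modifications (particularly, respiratory function) may be particularly associated with MsH", but MsH are scored on the return paths, after the distractor walk. Direct contamination is confined to the outward leg.
- *That breakdowns fall unequally across groups.* Nothing suggests it. A bias would need that, or a larger load effect in one group, which is plausible for MCI but not shown.
- *That flash cards are harder or easier.* The text does not say whether they carry words or pictures. With words, little but the medium changes.

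Two further points stand in part. If the experimenter's phone fails, the Howdy reports may be missing rather than distorted, since that phone carries both the list and the app. And section 2.4 names no analysis of the landmark score, although its correlations with DNT-mv results could include it.

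Finally, recording the mode and a sensitivity analysis are details that a condensed article may leave to the full protocol. Their absence is not the point here. The point is the substitute procedure that the article does state.

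**Conclusion.** The stated fallback is not equivalent to the planned procedure. The distractor differs clearly in cognitive load, and the landmark test possibly in format. Affected participants' landmark scores and outward-leg gait and cardiorespiratory data may not be comparable with the rest. Their later WTs and MsH may be affected through encoding, possibly more so in MCI.

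The size is unknown because no breakdown rate is given. With an assumed 10 to 30% of a group on the fallback and an assumed effect of 0.3 to 0.8 SD, the cases above give a bias of 0 to about 0.16 SD in a group contrast. If breakdowns are rarer, it is smaller. This is a minor point, worth acting on because the remedy is cheap. It does not show that the group comparisons or the prediction of real-world performance are invalid.

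**What to change.** - Make the backup like-for-like: print the same written landmark list with the same distractors in random order, and replace serial sevens with a target-detection task using the same shapes at the same 15 s pace.
- Record for each participant which mode was used for the distractor and for the landmark test.
- Repeat the main DNT-mv and physiological analyses without fallback-mode participants.

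The cost is some printing, a tick-box and one extra analysis, with no added staff or visits. The downside is that shapes shown on cards still differ somewhat from a worn watch: the participant must look towards another person, which may itself affect gait or attention. That is why the mode should be recorded even with the better backup. The article gives 29 February 2024 as the end of recruitment. If testing is already complete, only the record of mode, as far as it can be reconstructed, and the sensitivity analysis remain available.
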